## Abstract

**Background:**

Thailand is one of the most rapidly aging countries in Asia. Traditional family-based care, which has been the basis of most care for older people, is becoming unsustainable as families become smaller. In addition, women tend to be adversely affected as they still form the bulk of caregivers for older people, and many are likely to exit the labor market in order to provide care. Many family caregivers also have no or minimal training, and they may be called upon to provide quite complex care, increasing the proportion of older people receiving suboptimal care if they rely only on informal care that is provided by families and friends. Facing the increasing burden of noncommunicable diseases and age-related morbidity, Thai communities are increasingly in need of community-integrated care models for older persons that can link existing health systems and reduce the burden upon caring families. This need is common to many countries in the Association of Southeast Asian Nations (ASEAN).

**Objective:**

In this study, we aimed to assess the effectiveness of a community-integrated intermediary care (CIIC) model to enhance family-based care for older people.

**Methods:**

This paper describes a cluster randomized controlled trial comprised of 6 intervention clusters and 6 control clusters that aim to recruit 2000 participants in each arm. This research protocol has been approved by the World Health Organization Ethics Review Committee. The intervention clusters will receive an integrated model of care structured around (1) a community respite service, (2) the strengthening of family care capacity, and (3) an exercise program that aims to prevent entry into long-term care for older people. Control group clusters receive usual care (ie, the current system of long-term care common to all provinces in Thailand), consisting principally of a volunteer-assisted home care service. The trial will be conducted over a period of 2 years. The primary outcome is family caregiver burden measured at a 6-month follow-up, as measured by the Caregiver Burden Inventory. Secondary outcomes consist of biopsychosocial indicators including functional ability, as measured using an activity of daily living scale; depression, as measured by the Geriatric Depression Scale; and quality of life of older people, as measured by the EuroQol 5-dimensions 5-levels scale. Intention-to-treat analysis will be followed.

**Results:**

The CIIC facility has been established. Community care prevention programs have been launched at the intervention clusters. Family caregivers are receiving training and assistance. However, the COVID-19 pandemic delayed the intervention.

**Conclusions:**

Since ASEAN and many Asian countries share similar traditional family-based, long-term care systems, the proposed CIIC model and the protocol for its implementation and evaluation may benefit other countries wishing to adopt similar community-integrated care models for older people at risk of needing long-term care.

**Trial Registration:**

Thai Clinical Trials Registry TCTR20190412004; http://www.thaiclinicaltrials.org/#

**International Registered Report Identifier (IRRID):**

DERR1-10.2196/20196

## Introduction

### Background

Thailand’s population is estimated to be the third most rapidly aging in the world [1]. While it has a strong health system with a well-established system of universal health coverage, Thailand still needs to develop a long-term care (LTC) system and LTC insurance program. Policies are also needed to sustainably finance an effective LTC model for an estimated 11 million older people in 2020 [2]. Family-based, long-term care (FLTC) is the current model for the majority of LTC in Thailand.

Families form the backbone of the LTC system, a trait that is common to many Southeast Asian countries [3]. However, as families become smaller in Thailand, the sustainability of FLTC is challenged by human resources and its suitability as the technical needs for the care of older people become more complex. Vastly differing levels of education and care competencies found within family caregivers may cause inequalities in the care of older people across lower-resource and lower-income countries [4]. Furthermore, increasing caregivers’ burden and opportunity cost pose a key challenge to fast-aging countries where informal care in FLTC is the backbone of aging care. Such burden leads to job loss of the caregivers, abuse of older persons, and caregiver burnout. Interventions promoting the care capacity of informal care in FLTC become essential. Moreover, community-integrated respite service is required to reduce caregivers’ burden, sustain FLTC, and promote both older persons’ and caregivers’ health.

Among the Asian countries except Japan, FLTC is the common choice for most older adults. In some cases, it may be the only choice [3,4]. Recent literature reports studies of LTC models that are well established in high-income countries and compared them to the system of informal family caregiving in many Asian countries such as Thailand [4,5]. Aging and LTC in low-income Asian countries are insufficient for institution-based care and facilities, with policies tilting more towards relying on families and unpaid caregivers. However, many studies reported that FLTC in Asia had a greater positive impact on the psychosocial well-being of older adults [4,6].

In Thailand, as in many Association of Southeast Asian Nations (ASEAN) countries, families, particularly adult children, play a major role in giving care to older adults [3]. There are challenges to FLTC in the context of the Thai society. Adult children may migrate to work in geographically distant places, and concurrently, the sizes of families are in decline [7,8]. Moreover, the FLTC model prevents women and carers from entering the labor force and can place significant unmitigated burden and stress on those providing care. Based on predictions of increasing burden on family caregivers [6,7] it is important to strengthen the traditional FLTC model by initiating a feasible, formal LTC service and care prevention program.

If the weakness in FLTC in terms of technical and professional needs can be strengthened through community-based innovation, the results could be reduced burden of family caregivers, a positive impact on the biopsychosocial outcomes of older adults, and potentially improved healthy aging in communities. Therefore, research assessing the efficacy of innovative LTC models that are contextually relevant is urgently required to assist policymakers who will need to create evidence-based policies to strengthen or build LTC systems including FLTC.

In the context of limited facilities for LTC amidst a growing population of older people, intermediary care models can be an attractive option [9]. A recent study in Australia reported the promising impact of intermediary care centers on reducing family burden and improving the well-being of older adults [10]. This study suggested that intermediary care service with early detection and preventive services may be cost-effective.

Whether the presence of a community-integrated intermediary care center in a district can reduce the burden of family caregivers and promote the functional ability and quality of life (QOL) of older adults in the communities of Thailand is an interesting research question that has not yet been researched systematically. This study aims to assess the efficacy of a community-integrated intermediary care (CIIC) model and compare it to the existing traditional family care model in Thailand.

The CIIC model (Figure 1) is carefully designed to link the existing health care system and services in Thailand to the LTC needs of older people. The screening activity of the CIIC aims to screen for dependency and continually assess family caregiver burden, which could detect early low-level care needs and thereby prevent the future need for more intensive LTC.

**Figure 1 figure1:**
[figure not shown]
Conceptual framework of the Community-Integrated Intermediary Care (CIIC) model for older persons. UHC: universal health coverage scheme.

In Thailand, when environmental alterations are required to accommodate the needs of an older person, such as house management, handrails, and toilet and bathing modifications, district and local municipal funds usually support these needs. If older adults need assistive devices for instrumental activities of daily living (ADL), such as wheelchairs and walking sticks, there is an insurance scheme supported by national taxation (Figure 1). The proposed CIIC service will identify those who are in need and link these older people and their families to existing funds and providers. Moreover, community-based screening activities may identify persons with hypertension, diabetes, and other medical problems. The CIIC team can refer these individuals to the primary health care unit or the community hospital where all Thai citizens can access medical care as part of universal health coverage under the national health insurance program.

Recent policy in Thailand tends to support local governments in setting up centers for aging and LTC through social security insurance. This bill was passed to support municipal governments in the provision of LTC. Additionally, local governments also have their own budgets. However, there is a gap between the FLTC system and its integration with community-based health and LTC services that are managed by local government and municipalities. CIIC is expected to provide a model filling this gap (Figure 1)**.**

### Study Hypothesis, Objectives, and Rationale

#### Hypothesis

Improved competencies of family caregivers may reduce their stress and burden and promote the well-being of older adults as well as increase caregivers’ productivity. Functional training exercises for older people will preserve active aging whereas better home care will prevent LTC needs and hospitalization and could decrease health care costs. We hypothesized that there will be differences between the intervention clusters utilizing CIIC services and control clusters in terms of family caregiver burden, functional ability of the older persons, and their QOL.

Such an intervention will be evaluated in a randomized controlled trial, but individual randomization is not realistic and threatens the validity of the results by contamination. Therefore, a clustered randomized controlled design will recruit eligible villages and consented community residents, older persons, within the village as a cluster.

#### Objectives

This study aims to assess the effectiveness of a CIIC facility and its functions to assist families providing LTC for older adults in terms of reducing caregivers’ burden as the primary outcome. Another objective is to evaluate the effectiveness of the CIIC model in terms of the following secondary outcomes: impact on ADL, depression, and QOL of older people.

## Methods

### Trial Design

This is a 2-arm, parallel-design, interventional study designed as a cluster randomized controlled trial. A total of 4000 participants will be recruited in 12 clusters, 6 in the intervention group with 2000 older adults and 6 in the control group with 2000 older adults in Chiang Mai province, Thailand.

The unit of randomization, cluster, is a village. Participants in intervention clusters will receive the CIIC intervention after screening for eligibility. The eligibility criterion for a cluster is a village that has more than 300 older persons over 60 years of age at the time of randomization.

### Inclusion Criteria for Study Participants

The inclusion criteria are >60 years of age, has a family caregiver(s), either male or female, and resident in study site districts.

### Exclusion Criteria

People with the following characteristics will be excluded: lack of informed consent by those >60 years old or their family caregivers, cannot understand the explanation for informed consent despite being provided with language support, in a household without an older person >60 years old, or cognitive impairment or severe impairment of decision-making abilities.

### Study Setting

Chiang Mai, Northern Thailand is the location of the study. There are 284,457 older adults in Chiang Mai city according to the 2019 provincial report. Older adults account for 18% of the population, which is higher than the national proportion of people ≥60 years old (16%). Chiang Mai is culturally similar to many neighboring ASEAN countries in terms of caring for older parents as a family tradition and social value.

Two subdistricts involved in the study, sub-district XXX (10 villages) for intervention and subdistrict YYY (15 villages) for control, are in the same Muang Chiang Mai district of Chiang Mai province. They are geographically distant from each other. They have similar demographic and sociocultural characteristics. Both subdistricts have a similarly sized population (>18,000 people), with similar aging rates (>18% of the population is >60 years old), according to local population statistics. People in both subdistricts are mostly Thai people who have access to health care services through the national health insurance system and social welfare services for older people covered by municipality funds.

### Intervention

The intervention consists of (1) screening and assessment of family burden and LTC capacity, (2) care capacity building for family caregivers, (3) care prevention and functional training for older adults, and (4) a respite care service for families with caregiving difficulties.

#### Care in Both Arms

In both arms, a basic health check, blood pressure check, and BMI assessment will be provided for the study participants. If any disease is suspected through the health check, appropriate referrals to existing health care services will be provided. This is considered a benefit for all study participants. The control group will receive the same assessment with an explanation that the assessment is being conducted as part of a survey and the result will be utilized for research purposes. They also receive the benefit of the additional health check followed by appropriate referrals to health care professionals. Control arm participants will receive usual care (ie, the current system of LTC common to all provinces in Thailand), consisting principally of a volunteer-assisted home care service in addition to traditional family-based home care. The differences between the 2 arms are the newly launched CIIC services, as described in the following sections.

#### Screening and Assessment of Family Burden and LTC Capacity

After obtaining informed consent, screening of the families will be conducted to assess the capacity for and burden of caregiving for each family with older adults. All older adults and caregivers in each cluster who have provided informed consent will be screened for ADL status and health-related QOL utilizing the EuroQol 5-dimensions 5-levels (EQ-5D-5L) for older adults, and caregiver burden will be measured with the Caregiver Burden Inventory (CBI). The results will be utilized as a baseline assessment from which to measure the overall impact of the CIIC center.

#### Care Capacity Building for Family Caregivers

Based on the screening, a caregiving capacity building educational program will be provided to the family caregivers of dependent older adults (Table 1), based on the results of a recent study that indicated challenges with FLTC are due to a lack of education and technical competencies of family caregivers [11].

**Table 1 table1:** Content of the capacity building and training in the Community-Integrated Intermediary Care (CIIC) service model.

Category	Households with dependent older adults	Households with active or less dependent older adults
Whom to train	Family caregiver	Older adults
What to train	Prioritization of conditions for individually tailored care needs	Functional training to preserve functional ability and prevent the need for long-term care
How	Training delivered at home or can be group training, depending on the individual situation and specific care need	Group training 2 times a week as a care prevention exercise program
Who will train	CIIC nurse or assistant	CIIC nurse or assistant or invited experts such as a physical therapist or physical educationist

#### Care Prevention Exercise Program

Several exercise programs for preventing frailty and LTC will be provided to all the older adults in each intervention cluster (Table 2). The exercise program is based on a recent Japanese study that showed a positive, significant effect with 3 months of training on muscle strength, function, and cognitive [12,13]. A Japanese expert in this training will develop sets of exercises suitable for Thai older adults and train CIIC staff and community volunteers who will then become the trainers in the implementation of the study. Several awareness campaigns to motivate community older adults to become physically active will be conducted to increase access to the exercise program. Along with the implementation of the training, several physical functions (grip strength, flexibility, functional reach, static balance, walkability, and timed up and go tests) will be measured to assess the effect of the training.

The capability of participants to engage with the exercises will be screened before the training by a doctor or nurse. Blood pressure and heart rate will be measured, and a safety checklist will be completed as part of a safety assessment. Emergency response training or refresher courses such as for the provision of cardiopulmonary resuscitation and utilization of automated external defibrillator devices will be provided. The maximum size of one training class is 30 people. One session of training will comprise 10 minutes of stretching exercises, 30 minutes of functional training and exercises, followed by 10 minutes of cooling down and stretching. A total of 24 sessions (2 sessions per week for 12 weeks) will be provided.

The 30 minutes of functional training will entail a set of very light exercises for muscle flexibility as well as exercises to improve joint range to help maintain daily mobility and functioning. Very mild resistance training using soft rubber bands (Theraband) will be performed. It aims at maintaining and improving physical fitness especially for frailer older people and promotes personal exercise habits. This is one strategy for the prevention of the need for LTC.

Care-prevention exercises will be primarily delivered as community group exercise in each cluster in the intervention arm. In addition, participants will be offered an exercise poster, DVD, and safety instruction in order to practice the exercises at home.

In case the intervention proves to be beneficial, caregivers who could not access the study because the older person refused to participate will be informed that they can receive the training if they are still interested.

**Table 2 table2:** Tentative plan for a Community-Integrated Intermediary Care (CIIC) short-term stay at a respite care facility for older persons.

Type of staff	Number of staff	Function and services
Auxiliary nurses^a^	2	CIIC facility duty; coordination (arranging and scheduling screening and training), technical training of family caregiver for specific care needs, functional training to prevent a need for care
Nurse assistants	2	CIIC facility duty, care of older adults staying at the CIIC (meals, laundry, beds, and personal care), providing technical training for the family caregiver to provide specific care needs
Volunteers	30	Helping with the training of caregivers, social marketing of the CIIC to the community, psychosocial support, assistance with functional training, assisting CIIC staff

^a^These nurses are employed by this research project and are not seconded from the health system.

### Respite Care Service for Families Having Difficulties With Caregiving

In this project, intermediary care is defined as formal care that is neither day care nor a long-term residential service. It is a short-term residential service for older persons whose caregiver is temporarily unable to sustain care at home.

#### Registration

All the families assessed to be eligible for respite care services will be invited to register for the CIIC center’s temporary respite care services, which is not part of the primary health care center of the subdistrict. The services will be provided by newly established CIIC centers staffed with professional staff and volunteers who will provide assistance to family caregivers whenever they find it challenging to sustain caregiving of an older family member. The maximum length of stay is 10 days during the 6-month intervention. Our previous survey study found that 6.5% of older persons had decreased capabilities for ADL that required caregiver assistance [11]. Therefore, the estimated number of persons needing respite care is 130 people in a year; 50% (65/130) may be without a caregiver. These individuals will be provided with residential care; therefore, our calculations show that 5 beds would be sufficient for 10 persons at 2 weeks per year. This might not be enough beds during certain periods of the year. Therefore, a booking service will be provided.

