### CBI Criteria

On the assessment of caregiver burden, the following 2 eligibility criteria are required to utilize the respite care service: time dependency items score >17 and physical health items score >14.

If there is only one person in the family acting as a caregiver for the older adult with the qualifying ADL criteria and the caregiver has to leave the house to travel, the older adult would qualify for admission to the CIIC based on the available capacity of the facility on the appointment days.

These criteria can be revised by stakeholders depending on the estimates of the population to be served, budget of the municipality, and capacity of the facility.

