#### Primary Outcome

The primary outcome is the burden of family caregivers measured at a 6-month follow-up appointment. The CBI [14,15] will be applied to measure the family caregiver’s burden at baseline (month 0) and then again at month 6. CBI is an internationally well-validated measurement tool with a 24-item, 5-point Likert scale with the following 5 dimensions: time dependence burden (5 items), developmental burden (5 items), physical burden (4 items), social burden (5 items), and emotional burden (5 items).

The total scores will be summed, with total scores >36 indicating a risk of “burning out” whereas total scores >24 are considered indicative of “a necessity to seek some form of respite care.”

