### Sample Size

A sample of 4000 community-residing older adults will be recruited, with 2000 adults in each arm of the study (control and intervention), which our calculations show should suffice for the power required by the study. Including 1500 participants in each arm should be ample to detect the effect size difference of 0.5 unit with an SD of 4 between the 2 arms. STATA version 11SE (Stata Corporation, College Station, TX) was utilized for sample and power estimations. The precision levels applied are a *P* value of .05 with a 95% confidence interval. The sample size is inflated (1) for a design effect of 1.2 for applying a cluster randomized design and (2) to compensate for potential nonresponses and drop-outs of up to 20% during recruitment and the study. After inflation, a total sample size of 4000 is estimated to be required for the study. Moreover, the sample size will be sufficient for the estimation of key parameters such as mean CBI, ADL, and health-related QOL indicators in the study population.

There will be 6 clusters in each arm. The cluster size is in the range of 300-350. Within each cluster, individual participants meeting eligibility criteria will be recruited consecutively. Informed consent will be requested from a representative of each cluster before randomization and from each older participant and a family caregiver after randomization.

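### The planned 0.5-unit effect is averaged over all caregivers, while the components aimed at burden reach only households with dependent older adults, about 6.5% by the protocol's own figure

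*Protocol article*

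**What the plan says.** All places are in the protocol article.

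- **Who is enrolled and measured.** Inclusion Criteria ask only for age over 60, a family caregiver and local residence, with no threshold of dependency or burden. Under Screening and Assessment, every consenting caregiver has the CBI and every consenting older adult the ADL assessment at baseline.
- **What is compared.** "The primary outcome is the burden of family caregivers measured at a 6-month follow-up appointment" (Primary Outcome). Statistical Methods compare the CBI between arms by intention to treat, without restricting to dependent households.
- **Who gets what.** Caregiver training "will be provided to the family caregivers of dependent older adults" (Care Capacity Building). In households with active or less dependent older adults, Table 1 trains the older adult, not the caregiver. Respite requires help with at least two of six ADL plus CBI thresholds (ADL Criteria, CBI Criteria). The exercise programme is for all older adults in the intervention clusters.
- **Which components act on burden.** Secondary Outcomes names the respite home and caregiver training as aimed directly at burden, and gives this as the reason for the choice of primary outcome.
- **How many are dependent.** Registration cites an earlier survey: "6.5% of older persons had decreased capabilities for ADL that required caregiver assistance". It derives 130 people a year, of whom half (65) may have no caregiver.
- **What was powered.** "Including 1500 participants in each arm should be ample to detect the effect size difference of 0.5 unit with an SD of 4" (Sample Size). The scale is not named.

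**The concern.** The outcome was chosen because two components act on it directly, yet those components reach a small minority of the people over whom it is averaged. An arm mean then shows the minority's benefit multiplied by its share, plus whatever the majority gains. The planned 0.5 looks modest as a cohort average. It may be a large demand on the households that receive training or respite, and the sample size section does not say which is meant.

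At stake is the reading of the result. A worthwhile reduction in burden among caregivers of dependent older adults could yield a small, non-significant cohort mean. The Objectives section frames the aim around families who provide long-term care, so readers will want to know what happened to those families.

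**Working it through.** **1. The plan's own figure.** Inputs from Sample Size: difference 0.5, SD 4, "The precision levels applied are a *P* value of .05 with a 95% confidence interval", inflation "for a design effect of 1.2 for applying a cluster randomized design", and 20% loss. Power and sidedness are not stated; I take two-sided testing.

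- n per arm = 2 × (1.96 + z)² × 4² / 0.5². At 90% power this is 1345.
- 1345 × 1.2 = 1614, and 1614 / 0.8 = 2018 per arm, or 4036 in total. That is within 1% of 4000.
- Other powers fit less well: 80% gives 3016, 85% gives 3450 and 95% gives 4992.
- The intermediate 1500 is not the uninflated n at 90%; inflating it the same way gives 2 × 1500 × 1.2 / 0.8 = 4500.

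So 4000 is reproducible as a 90% power calculation for one homogeneous 0.5-unit effect.

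**2. Share with dependency.** 0.065 × 2000 = 130, matching Registration.

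**3. Dilution.** Arm-mean effect = p × d(dependent) + (1 − p) × d(others). With p = 0.065, solving for the effect needed in dependent households gives (0.5 − 0.935 × d(others)) / 0.065:

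| Gain in all other caregivers | Needed in dependent households |
|---|---|
| 0 | 7.7 |
| 0.1 | 6.3 |
| 0.25 | 4.1 |
| 0.4 | 1.9 |

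With no gain elsewhere but a different enrolled share: 10% gives 0.5/0.10 = 5.0, and 20% gives 2.5. If the 65 people without a caregiver cannot enter, the share is 65/1935 = 3.4% and the figure is 0.5/0.0336 = 14.9.

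**4. Power of the whole-cohort mean on the plan's own terms.** SD 4, effective n = 2000 × 0.8 / 1.2 = 1333 per arm, 6.5% dependent, no effect elsewhere:

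| Effect in dependent households | Arm-mean effect | Power |
|---|---|---|
| 2 | 0.13 | 13% |
| 4 | 0.26 | 39% |
| 5 | 0.325 | 55% |
| 7.7 | 0.50 | 90% |

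**5. Is SD 4 plausible for such a mix?** A gap g between the group means alone contributes g × √(0.065 × 0.935) to the SD. This reaches 4 at g = 16.2 and 5.9 at g = 24. The protocol gives no CBI distribution, so this is a reason to check the SD, not proof that it is wrong.

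**6. What a dependent-dyad comparison could detect.** Assumptions, none from the protocol: SD 12 to 15 in dependent dyads and 3 to 5 in the others, 6 villages per arm, ICC 0.01 in the subgroup, t test on 10 df. The subgroup has 130 × 0.8 = 104 completers per arm, or 65 × 0.8 = 52 if half cannot enter.

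- Subgroup design effect at 104: 1 + (104/6 − 1) × 0.01 = 1.16. At SD 12, SE = 12 × √(2 × 1.16/104) = 1.8.
- Whole cohort, same mixture, with the mean gap between groups removed by adjustment: SD = √(0.065 × 12² + 0.935 × 3²) = 4.2, up to 6.2 with SDs of 15 and 5. With the plan's design effect, SE = 4.2 × √(2 × 1.2/1600) = 0.16, up to 0.24.

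| Effect in dependents | Subgroup, 104 per arm | Subgroup, 52 per arm | Whole cohort, adjusted |
|---|---|---|---|
| 3 points | 23–33% | 14–20% | 11–19% |
| 4 points | 36–52% | 22–32% | 17–30% |

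The whole-cohort column uses a share of 6.5% and so pairs with 104 per arm. It must not be set against step 4, which takes an overall SD of 4.

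**The case against.** The strongest reply is that the trial tests a community programme. Background asks whether the presence of a centre in a district reduces burden, the exercise programme reaches all older adults, and preventing dependency is one of the intended mechanisms. A whole-cohort intention-to-treat mean is a legitimate answer to that question, and restricting to baseline dependents would exclude prevention. This stands, and it is why the primary estimand should not be replaced. A reader might infer that a null result could not answer the trial's question; the protocol does not support that.

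Second, 7.7 is conditional. Nothing in the protocol says that other caregivers gain nothing, and a gain of 0.25 there nearly halves the figure. The 6.5% comes from a survey of older persons, whereas the trial enrols only those with a family caregiver; Table 1 does not define dependent households by that 6.5%. All this stands, so the figure needs its range. It is equally unsupported to say that the other caregivers sit near the bottom of the scale.

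Third, subgroup analyses belong to a statistical analysis plan that is not shown. True, and their absence is not the complaint. The complaint is a sample size that fixes one effect over a mix which the same article describes.

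Fourth, it is tempting to set very low whole-cohort power against very high subgroup power. Such a contrast depends on an assumed CBI distribution, a chosen ICC and the full 7.7-point benefit in dependents. At 3 to 4 points neither analysis is strong.

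Finally, a reader might see a contradiction between the respite thresholds ("time dependency items score >17 and physical health items score >14") and the statement that "total scores >24 are considered indicative of" a need for respite. The latter interprets a score. The former ration a small facility and are stated to be open to revision. They do not bear on dilution.

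**Conclusion.** The point holds in conditional form. The primary CBI mean covers all enrolled caregivers, the components that the protocol says act directly on burden go to dependent households, and the sample size does not allow for this. If benefit is confined to 6.5% of dyads, the planned 0.5 implies about 7.7 points in them. Plausible changes to the share or to the gain elsewhere move that from about 2 to about 15. On the plan's own SD and design effect, a 4-point benefit confined to dependents would be detected with 39% power, not 90%.

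This rests on three things outside the text: that the survey share carries over to the enrolled dyads, that gains elsewhere are small, and that the 0.5 unit and SD of 4 are on the CBI. The last is an inference from the CBI being the sole primary outcome. If they are on another scale, the primary outcome has no stated power basis.

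**What to change.** 1. Keep the whole-cohort intention-to-treat CBI mean as primary, adjusted for baseline CBI and baseline ADL dependency. Both are measured before launch in both arms, and Statistical Methods already foresees a random effects model with individual-level covariates.
2. Before outcomes are examined, pre-specify as first key secondary the CBI comparison in dyads whose older person needed ADL help at baseline on the Barthel Index, with a dependency-by-arm interaction. Fix the Barthel definition in advance. Respect village-level clustering in both.
3. State the scale to which the 0.5 unit and SD of 4 refer, report the enrolled share with dependency, and check the SD against the baseline CBI data.

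The cost is analysis work only; no new data are needed. Timing matters: Results puts the end of implementation at December 2020 and evaluation by March 2021. If outcomes have already been seen by arm, the subgroup comparison must be labelled post hoc. The subgroup is small, about 50 to 130 dyads per arm, with limited power for effects of 3 to 4 points, and its result applies only to caregivers of dependent older adults.
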